#### Main secondary outcomes

A set of secondary outcomes clinically relevant for the elderly populations was established, including diastolic BP, endothelial function, and cardiorespiratory fitness. Together with systolic BP, the diastolic BP will be assessed through ambulatory and ‘at office’ measurements. Endothelial function is determined by flow-mediated dilatation measured by high resolution ultrasonography at baseline, mid-intervention (6 weeks), and post-intervention (12 weeks), in agreement with published guidelines [17]. Due to resource availability, this outcome is assessed only in participants allocated at the coordinator center. Cardiorespiratory fitness is determined by peak oxygen consumption (VO_2_peak) obtained by maximal cardiopulmonary exercise testing at baseline and 12 weeks. Data regarding both main secondary outcomes will be aggregated as group means at the measurement timepoints.

#### Other outcomes

Other outcomes include complementary measures of physical function, habitual physical activity, adherence to pharmacological therapy, quality of life, and autonomic function. Physical function is evaluated by: (1) total walking distance, as assessed by the six-minute walk test [18], expressed as the longest distance walked at baseline and 12 weeks; (2) lower-limb functional capacity assessed by the Short Physical Performance Battery (SPPB), expressed by scores from 0 (worst performance) to 12 (best performance) based on 3 standing balance tests of increasing difficulty, five sit-to-stand attempts, and a 3-m walk test; and (3) handgrip strength, measured by a hand dynamometer. Self-reported physical activity is measured by the International Physical Activity Questionnaire (IPAQ) [19]. Medication adherence is assessed by Morisky’s 8-item adherence scale (MMAS-8) [20–23]. Quality of life (QoL) outcomes are evaluated by: (1) geriatric depression symptoms, as assessed by the total score on the 15-item geriatric depression symptoms scale (GDS-15) [24, 25]; and (2) scores of QoL, as assessed by the World Health Organization Quality of Life questionnaire (WHOQoL-OLD) [26]. In addition, participants allocated at the coordinator center undergo an autonomic modulation assessment by beat-to-beat BP variability and heart rate variability analysis at rest sympathetic stimulation with the Stroop Color-Word Conflict Test.

#### Safety outcomes

The harms occurring over the period of participation in the trial are defined as adverse events as established by the National Institutes of Aging [27]. Such events are classified according to their severity (mild, moderate, severe), predictability (expected or unexpected), and potential relation with study procedures (definitely related, possibly related, or unrelated). We collect and manage solicited and spontaneously reported adverse events. There is no fixed collection schedule for assessment of harm outcomes, however, spontaneous reports have been documented, communicated to the IRB and managed at demand. In addition, triggers for inspection include absence to one intervention or measurement sessions.

There is no formal adjudication committee, but adverse events are discussed and, if necessary, adjudicated by at least four (50%) out of the following investigators: principal investigator. ([name]), study director ([name]), study medical director ([name]), study managers ([name], [name], [name]), and expert consultants ([name], [name]).

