**Methods:**

Randomized, single-blinded, multicenter, two-arm, parallel, superiority trial.

A total of 184 subjects (92/center), ≥60 years of age, with no recent history of cardiovascular events, will be randomized on a 1:1 ratio to 12-week interventions consisting either of a combined exercise (aerobic and strength) training, three times per week, or an active-control group receiving health education intervention, once a week. Ambulatory (primary outcome) and office blood pressures, cardiorespiratory fitness and endothelial function, together with quality of life, functional fitness and autonomic control will be measured in before and after intervention.

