### Interventions

The HAEL participants are randomly allocated either to a combined exercise training program or to a health education intervention, each lasting 12 weeks. Detailed description on both interventions is provided below:

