#### Strategies for trial retention

During weekends, participants allocated to both groups receive text messages with Institutional Review Board (IRB)-approved content to reinforce time and place of intervention sessions. For the health education group, the message content is based on the topic that will be covered at the next class, whereas the exercise training group receives four slightly different messages along each month of intervention (three monthly cycles of four messages). We use phone calls to inquire for any adverse events if a participant misses a session of any intervention arm. The phone calls schedule is ceased for participants declaring their withdrawal from the study.

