### Adherence assessments

Measures of adherence to interventions will be reported as group averages and operationalized as attendance and compliance. Attendance is monitored through session’s frequency recording and will be treated as the percent of intervention sessions experienced by a participant given the total number of scheduled sessions (36 sessions for the exercise program or 12 sessions for the education program). Adherence will be treated as the percent of intervention sessions fully accomplished without protocol deviations given the total number of scheduled sessions. For example, this may include either: (i) a participant allocated to the exercise program that, for any reason, walked less than the prescribed duration for a given session; or (ii) a participant allocated to the education program that only partially watched a lecture.

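### Harms have no fixed collection schedule and depend on reports and absence-triggered calls, so with 36 versus 12 scheduled sessions, arm-level counts of short or mild events are liable to be inflated under exercise

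*Protocol article*

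**What the plan says.** The Safety outcomes section says of timing: "There is no fixed collection schedule for assessment of harm outcomes, however, spontaneous reports have been documented". It adds that "We collect and manage solicited and spontaneously reported adverse events" and that "triggers for inspection include absence to one intervention or measurement sessions".

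The solicited route is spelled out under Strategies for trial retention: "We use phone calls to inquire for any adverse events if a participant misses a session of any intervention arm". The same section ends: "The phone calls schedule is ceased for participants declaring their withdrawal from the study".

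Table 3, the time scheme, has rows for the efficacy and control measurements but none for adverse events. It does place both arms at a 6th-week evaluation visit and at final evaluation visits.

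Adherence assessments gives the scheduled totals as "36 sessions for the exercise program or 12 sessions for the education program". The Interventions section has blood pressure measured before every exercise session (values documented once a week) and before each weekly education session.

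Two other places bear on withdrawals. The Outcomes section invites drop-outs to the end-of-study assessment. Statistical considerations plans to record the reasons for each withdrawal individually.

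**The concern.** The call rule reads the same for both arms, but it is tied to sessions, and the arms differ in sessions by design. A participant who is due three times a week has more chances to miss a session and be called, and more chances to mention a symptom to staff, than one who is due once a week. Two arms with the same true rate of minor events could then show different recorded rates.

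Harms are a named outcome, the Discussion calls the trial confirmatory, and there is no data monitoring committee. A harms table by arm will be read as a comparison whether or not a test accompanies it. The Discussion defends the unequal weekly frequency on grounds of repetition and attrition, and does not consider its effect on recording harms. Participants and session staff are also unblinded, so blinding gives no protection against differential reporting.

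**Working it through.** **Inputs from the protocol article.** Weekly frequency: "three times per week, or an active-control group receiving health education intervention, once a week" (abstract, Methods). Duration: "each lasting 12 weeks" (Interventions). The document gives no attendance or reporting probabilities, so those below are assumptions shown over a range.

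**1. Reproduce the session totals.** 3 × 12 = 36 and 1 × 12 = 12. Both agree with Adherence assessments. The ratio is 36 / 12 = 3.0.

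**2. Absence-triggered calls at equal attendance.** With absence probability *a* per session and one call per missed session, expected calls are 36*a* and 12*a*. With independent absences, the chance of at least one call is 1 − (1 − *a*)^n.

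| *a* (assumed, both arms) | Calls, exercise | Calls, education | At least one, exercise | At least one, education |
|---|---|---|---|---|
| 0.05 | 1.8 | 0.6 | 84% | 46% |
| 0.10 | 3.6 | 1.2 | 98% | 72% |
| 0.20 | 7.2 | 2.4 | >99.9% | 93% |

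**3. Unequal attendance.** The call ratio is 3 × (absence in exercise / absence in education). With 10% absence in exercise and 30% in education (assumed), calls are 36 × 0.10 = 3.6 and 12 × 0.30 = 3.6, a ratio of 1. The 3:1 ratio of calls is therefore conditional on attendance.

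**4. Illness that keeps a participant away.** Assume sessions on days 1, 3 and 5 of the week versus day 1 only, and an illness equally likely to start on any of the seven days. The chance that it covers at least one session, and so triggers a call, is:

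| Days away | Exercise | Education |
|---|---|---|
| 1 | 3/7 = 43% | 1/7 = 14% |
| 3 | 7/7 = 100% | 3/7 = 43% |
| 5 | 100% | 5/7 = 71% |
| 7 | 100% | 100% |

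The imbalance is largest for one-day illness and disappears at seven days.

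**5. Event that does not keep the participant away.** For an event lasting one week, with probability *q* of being mentioned at each session attended, capture is 1 − (1 − *q*)³ in exercise and *q* in education.

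| *q* (assumed) | Exercise | Education | Apparent risk ratio at equal true risk |
|---|---|---|---|
| 0.3 | 66% | 30% | 2.2 |
| 0.5 | 88% | 50% | 1.75 |
| 0.7 | 97% | 70% | 1.4 |

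Longer events narrow the gap. Over two weeks at *q* = 0.5, capture is 1 − 0.5⁶ = 98% versus 1 − 0.5² = 75%, a ratio of 1.3.

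**6. After the change.** With one enquiry at week 6 and one at the final assessment, scheduled solicited enquiries are 2 versus 2 per participant, a ratio of 1.0.

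**The case against.** Several points on the other side are fair.

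- **Attendance.** Only scheduled sessions are known to be 3:1. Calls depend on absence, and step 3 shows that they could be equal. This stands, and is why the point is worded for similar attendance.
- **Session contact as a prompt.** The Safety outcomes section names spontaneous reports and absence. It does not say that reports are made to session staff. That is an inference from in-person sessions and the blood pressure checks. It is reasonable, but still an inference.
- **Solicited events and unseen procedures.** The section mentions solicited events, missed measurement visits (common to both arms) also trigger enquiry, and Harms refers to an ethics-approved algorithm that is not shown. The article may condense a fuller procedure. Even so, its statement that there is no fixed schedule is explicit, not an omission.
- **Withdrawals.** A reader might infer from the end of phone calls that harms behind withdrawal are simply lost. The documents do not support that: reasons for withdrawal are to be recorded case by case and drop-outs are invited to the final assessment. What remains is narrower: no common harm question is described for them.
- **No planned safety test.** No formal between-arm comparison of harms is specified, and the primary outcome is untouched. The point concerns how counts by arm would be read.

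A reader might also try to fix the size of the bias by treating every session as an independent chance to detect an event present for all 12 weeks. With chances of 2%, 5% and 10% per contact, that gives ratios of 2.4, 1.8 and 1.4. At 30% the same formula gives over 99.9% versus 98.6%, a ratio of about 1.01. The answer is set by the assumed probability, and most events do not last 12 weeks, so such ratios are not estimates for this trial.

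**Conclusion.** The point holds in limited form. As written, the plan gives the two arms unequal opportunity to record short or mild harms: about three to one at similar attendance, with the excess expected in the exercise arm. Hospitalizations and illnesses lasting a week or more are less affected.

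The document does not allow the size to be computed. The apparent ratios of 2.2 to 1.4 in step 5 are illustrations that rest on a one-week event and assumed reporting probabilities. The stronger conclusion, that the trial's safety comparison is biased by a known factor or that it can say nothing on comparative safety, is not supported. Attendance by arm is unknown, serious events have other routes to notice, and no formal comparison is planned. The matter should be corrected because it touches a named outcome and the remedy is small, but it does not threaten the primary result.

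**What to change.** Add an adverse-event row to Table 3 at the 6th-week visit and at the final evaluation, and amend Safety outcomes to match. Ask every randomised participant in both arms the same short questions over the same recall period, including drop-outs who attend the final assessment. Base any between-arm description of harms on these solicited events. Keep the spontaneous and call-triggered routes for participant safety, but tabulate what they yield separately, alongside the number of sessions attended and calls made in each arm.

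Because outcome assessors are blinded and participants are asked not to discuss their intervention with them, the form should be self-completed or taken by someone outside outcome assessment.

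The cost is a few minutes at visits that already take place, one form and a notification to the ethics board. More events will be recorded. Recall over about six weeks will miss some minor events, though the question and its timing will be the same in both arms. Recruitment began in September 2017, so participants who have already finished will have no solicited data and should be shown separately.

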### Outcomes

In each center, both randomized groups are assessed for the outcomes listed below by standardized methodological procedures and a similar schedule (Table 3). Outcomes are measured for all randomized participants, irrespective of attendance or completion status. For participants who drop out of the study at any time after the randomization, research personnel use contact information to invite such individuals to undergo the end-study outcome assessments (12 weeks after intervention onset).

**Table 3 Tab3:** Time scheme for study conduction

	Study period							
	Enrolment	Baseline measures	Allocation and run-in^*^	Post-allocation			Close out	
TIMEPOINT**➔**	t-1	t0	t1	t2	t3	t4^†^	t5^†^	t5^†^
*Timepoint description*	Interviews	Occurs in 2 or 3 evaluation visits	–	Intervention Start	Evaluation visit (6th week)	Intervention end	Final evaluation visit 1	Final evaluation visit 2
ENROLMENT:								
Eligibility screening	x							
Informed consent	x							
Allocation			x					
INTERVENTIONS								
Combined exercise program				x	x	x		
Health education program				x	x	x		
ASSESSMENTS								
*Primary outcome*								
Ambulatory blood pressure		x					x	
*Main secondary outcomes*								
Office blood pressure		x					x	
Endothelial function^‡^		x			x		x	
Cardiorespiratory fitness^§^		x						x
*Other outcomes*								x
6-min walking test distance		x						x
SPPB		x						x
Quality of life questionnaires		x					x	
Autonomic function^‡^		x					x	
*Additional measurements*								
Anthropometric measurements		x					x	
Medication adherence scale (MMAS-8 Questionnaires)		x					x	
Blood variables collection		x					x	
Self-reported physical activity		x			x		x	
Grip strength		x			x			x

*SPPB* Short physical performance battery; *MMAS* Morisky Medication Adherence Scale. * = run-in period will be no longer than 2 weeks. † = time between t4 and t5 will be no longer than 2 weeks. ‡ = analysis of blood pressure and heart rate variability, exclusive for data collected at the coordinator center; § = cardiorespiratory fitness assessment occurs in a third separate visit at the participating center. Use of the©MMAS is protected by US copyright and registered trademark laws. Permission for use is required. A license agreement is available from [name], [name]; [contact]

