Incomplete data will be explored in sensitivity analyses by pattern mixture model. This procedure will describe whether there is an interaction between the main missing patterns and other variables (e.g., group, time, group by time, BP status, BP status by group). We expect two main missing data patterns based on an indicator of completers versus non-completers (defined as randomized subjects without 12-week data). Because withdrawals may occur due to specific harms or other non-anticipated reasons, we will assess whether additional grouping (indicator) should be made due to different patterns of missing data. Therefore, we will qualitatively document reasons and details of withdrawals on a case-by-case basis. In the case of identifiable patterns indicating that missing data are nonignorable, the interpretation of related findings should take missingness into account. No interim analyses other than monitoring of demographic data are planned.

Continuous variables will be summarized according to intervention groups at baseline, if applicable, and end of trial using arithmetic or geometric means, standard deviations, ranges, and interquartile ranges as appropriate. Change from baseline will be summarized descriptively accompanied by its 95% CI. In descriptive summaries, last observation carried forward (LOCF) will be employed to impute missing values. Categorical variables at baseline and end of trial (if applicable) will be summarized as absolute number and proportion of subjects (%) according to intervention groups.

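### Harms have no fixed collection time and the described inquiries depend on absence, so recorded adverse events partly follow how often participants are contacted

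*Protocol article*

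**What the plan says.** All references are to the protocol article.

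- **Window and schedule (Safety outcomes).** "The harms occurring over the period of participation in the trial are defined as adverse events", but the section does not say when participation ends. It adds: "There is no fixed collection schedule for assessment of harm outcomes". Both solicited and spontaneous reports are collected, and "triggers for inspection include absence to one intervention or measurement sessions".
- **Calls (Strategies for trial retention).** "We use phone calls to inquire for any adverse events if a participant misses a session of any intervention arm". Then: "The phone calls schedule is ceased for participants declaring their withdrawal from the study".
- **Recontact (Outcomes).** "Outcomes are measured for all randomized participants, irrespective of attendance or completion status". People who drop out after randomization are invited back for the week-12 assessments. Table 3, which schedules items down to grip strength and questionnaires, has no row for adverse events.
- **Link between harm and exit.** Under Criteria for discontinuing allocated interventions, cardiovascular events, hospitalization and severe health events end participation in either arm. Muscle or joint injury does so in the exercise arm. Statistical considerations takes the same view: "Because withdrawals may occur due to specific harms or other non-anticipated reasons", reasons for withdrawal are to be documented case by case.

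**The concern.** Efficacy is to be measured at a fixed time in everyone randomized, but harms have no fixed time at all. Where inquiry depends on absence, the chance that a harm is recorded depends on how many sessions a person was due to attend, how many were missed, and whether the person had declared withdrawal. The arms differ threefold in scheduled sessions, so a table of harms by arm would mix true frequency with opportunity to report.

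The later course of a harm that caused someone to leave, and any harm that arises after a declared withdrawal, would rest mainly on spontaneous report. At stake is the safety comparison in a trial whose Discussion calls it confirmatory, and which has neither a data monitoring committee nor a formal adjudication committee. The efficacy result is not at stake.

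**Working it through.** The plan gives no figure for harms, so there is none to reproduce. The check sets the stated rules against the possible participant paths and then counts contact occasions.

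**Who meets a stated harm question**

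| Path | Stated prompt |
|---|---|
| Attends every session and week 12 | None |
| Misses a session, has not withdrawn | Phone call; inspection |
| Declares withdrawal, attends week 12 | None after exit |
| Declares withdrawal, stays away at week 12 | Absence from a measurement session may prompt inspection |

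At week 12 the stated trigger can therefore reach the withdrawer who stays away but not the one who attends. Table 3 also allows up to two weeks of run-in and up to two weeks between intervention end and final assessment. No intervention session falls in those gaps, so the missed-session call cannot operate there.

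**Scheduled contact by arm.** Adherence assessments gives 36 exercise and 12 education sessions. Each is either attended (a chance for spontaneous report) or missed (prompts a call). Ratio: 36 / 12 = 3.0.

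**Calls alone, before withdrawal** (scheduled minus attended sessions)

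- Full attendance: 0 v 0.
- Per-protocol threshold in Statistical considerations (25 and 8 sessions): 36 − 25 = 11 v 12 − 8 = 4. These are upper bounds, because a session attended but only partly completed fails adherence without being missed.
- 80% attendance, assumed equal in both arms: 36 × 0.20 = 7.2 v 12 × 0.20 = 2.4.
- 70% attendance, same assumption: 36 × 0.30 = 10.8 v 12 × 0.30 = 3.6.

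**After declared withdrawal:** 0 v 0 missed-session calls.

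**How many may leave.** Sample size allows 22 extra subjects for 10–15% dropout; 184 × 0.10 = 18.4 and 184 × 0.15 = 27.6. How many of these would declare withdrawal and still attend week 12 is not given, and neither is a harm rate. The counts above are occasions to record a harm, not harms lost.

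**Effect of one added week-12 question.** The question itself is 1 v 1. Total occasions become 36 + 1 = 37 v 12 + 1 = 13, and 37 / 13 = 2.85, so the overall imbalance remains.

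**The case against.** Several counter-arguments have force.

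- **The trigger list is open.** The section says that triggers include absence, and that solicited reports are collected. A reader might infer that harms are sought only when someone is absent; the text does not support that. What stands is that absence is the only prompt the article describes.
- **The week-12 visit.** A reader might infer that dropouts are recontacted for efficacy outcomes alone. Safety outcomes sits under the Outcomes heading, whose rule covers all randomized participants, so the rule may be meant to include harms. On that reading harms in dropouts are required, yet no time is set at which to ask.
- **Other safety contact exists.** Blood pressure is measured before every exercise session and before the weekly education sessions. Sustained values of at least 180 or 100 mmHg lead to a medical appointment within seven days in either arm (Hypertension management). A physician helps supervise the maximal exercise test. Withdrawal reasons should capture the harm that prompted exit. These are real safeguards, but none is described as a question about falls, injury, hospitalization or events after exit.
- **Documents not shown.** The manual of operating procedures and the adverse-event algorithm approved by the review board may contain a week-12 question. That limits the point to the rules stated here. It does not remove it, because the absence of a fixed schedule is stated outright.
- **Contact frequency follows from the interventions,** as the Discussion acknowledges, and one added question does not equalize it. This is correct and shapes the fix.

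Stopping missed-session calls after withdrawal is reasonable in itself.

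**Conclusion.** The point holds as a cheap improvement of minor to moderate weight. On the stated rules, harm ascertainment has no fixed time and an undefined window. No described question reaches full attenders or withdrawers who return at week 12. Recorded harms will therefore partly track contact, with 36 v 12 scheduled sessions before exit and no missed-session calls after declared withdrawal.

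A reader might go further and conclude that harms will be undercounted in a particular arm. The article does not support that. More contact in the exercise arm could raise its recorded count, while harm-driven exit could lower it, and neither a harm rate nor a count of returning withdrawers is given. The attendance figures of 70% and 80% are illustrations that assume equal attendance in both arms. The conclusion also assumes that the procedures manual and the adverse-event algorithm add no uniform week-12 inquiry.

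**What to change.** 1. **Safety outcomes:** define the adverse-event window as randomization to the week-12 assessment for all randomized participants, regardless of withdrawal or discontinuation.
2. **Week-12 contact, already planned under Outcomes:** have existing staff other than the blinded outcome assessor ask every participant in both arms the same harm question, including withdrawers who accept contact. Add the row to Table 3.
3. **Strategies for trial retention:** keep the stop on missed-session calls and state that it does not end adverse-event collection.
4. **Reporting:** present harms by randomized arm, with answers to the week-12 question shown separately from spontaneous and call-prompted reports. The first set rests on one equal occasion per arm; the second still reflects contact frequency.

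The cost is a definition, a clarifying sentence, one question and one split in a table, with no new visit and no change to the efficacy analysis. The downsides are recall over several weeks, no information on people who refuse contact, and a possible amendment through the review board. Recruitment began in September 2017, so participants already past week 12 cannot be asked in the same way. The report should say when the question was introduced.
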